## Data analysis

We expect to collect data from 48,960 patient episodes of care representing 244,800 bed days. With this sample, and with assumptions based on unpublished data for falls occasioning harm, pressure injuries and rapid response calls (intra-cluster correlation = 0.03–0.08, baseline rate = 2–8 incidents/1000 bed days) we will be powered to detect difference in the rate of incidents of 12–28% from pre- to post-intervention [30].

The data analysis period will extend across 68 weeks, comprising 51-week trial period and an additional 17-week control period prior to the first step (Fig. 2). All patients admitted or transferred to one of the study wards during the trial period will be included in the primary analysis. While outcome data are collected continuously, for analysis, time will be categorised per week. Days in weeks prior to the ward commencing the intervention will be counted as pre-intervention, with the exception of the three weeks immediately prior which will be omitted from the analysis as a period for implementation of the intervention (one week of nurses’ education workshops and two weeks of preparation). The three-year set of pre-trial primary outcome data will be used to investigate seasonal or temporal effects, or unusual variations in routinely collected data. Patient age, sex, comorbidity information and admission/transfer data will be used to adjust for variation in patient demographics between wards.

Patient outcome data will be modelled as counts using Poisson regression with an offset for time on ward. Using a Generalised Linear Mixed Model (GLMM) approach, we will use fixed effects for secular trend, and a random effect for ward. The primary outcome will be a composite measure of: (i) medical emergency team calls (inclusive of both rapid response system and ‘Code Blue’ calls); (ii) unplanned intensive care unit admissions; (iii) in-hospital falls; and (iv) hospital-acquired pressure injuries.

Patient, nurse and medical officer experience measures will be reported as means and standard deviations of overall component scores, and changes from pre- to post-intervention will be tested using a GLMM with a Poisson link function adjusting for respondent age, tenure (if appropriate) and correlation within ward. We will conduct secondary analyses: i) to investigate changes in outcomes over time, ii) perform the above with additional fixed effects for patient demographics (age, sex, comorbidity), and iii) model differences in primary outcome components by level of comorbidity. A statistical analysis plan pre-specifying all analyses will be formulated and finalized prior to the study data lock.

All analysis will be conducted in the R language for statistical computing, using the lme4 package for generalised linear mixed models [69].

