## Outcome measures

## Primary

The primary outcome will be a composite measure of: (i) medical emergency team calls (consisting of: a) rapid response system calls, i.e. patients identified as potentially/actually clinically deteriorating, and b) ‘Code Blue’ calls, i.e. medical emergency and cardiopulmonary arrest [30]), (ii) unplanned intensive care unit admissions (patients unexpectedly requiring transfer from participating wards to the intensive care unit), (iii) in-hospital falls, and (iv) hospital-acquired pressure injuries.

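### The stated 12–28% detectable difference fits a pre/post comparison with no time effect, not the planned stepped-wedge model, and no figure is given for the composite primary outcome

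*Protocol article*

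**What the plan says.** The sample size statement opens the Data analysis section: "We expect to collect data from 48,960 patient episodes of care representing 244,800 bed days". It then gives its assumptions ("intra-cluster correlation = 0.03–0.08, baseline rate = 2–8 incidents/1000 bed days") and the result, "we will be powered to detect difference in the rate of incidents of 12–28% from pre- to post-intervention". The outcomes behind it are named: "assumptions based on unpublished data for falls occasioning harm, pressure injuries and rapid response calls". Significance level, power, the scale of the ICC and which rate goes with which effect are not given.

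The same section fixes the analysis. It uses Poisson counts with an offset for time on ward, and for the mixed model "we will use fixed effects for secular trend, and a random effect for ward". The data cover 68 weeks: a 17-week control period and the 51-week trial. The three weeks before each ward starts are left out. The Design and Randomisation sections give 24 wards, eight hospitals, three sequences and 17-week periods.

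Under Outcome measures, the primary outcome is a composite of medical emergency team calls, unplanned intensive care admissions, in-hospital falls and pressure injuries. Its components are secondary outcomes.

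**The concern.** In a stepped-wedge trial the intervention is partly confounded with calendar time. On the layout described in the text, every ward is in control during the first 17 weeks and every ward is in intervention during the last 17. Once time is fitted, those periods offer no concurrent comparison, and the treatment contrast between wards comes from the two middle periods. A calculation framed as pre to post can treat all bed days as two groups and miss this loss.

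Two things are at stake. A non-significant component result would be read against a sensitivity of 12–28% that the planned model does not have. And for the primary outcome, a reader has no stated sensitivity against which to judge a null result.

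**Working it through.** **Inputs from the article.** 24 wards; three sequences (taken as eight wards each, one per hospital); 68 weeks in four 17-week periods; three weeks omitted per ward; 244,800 bed days; 2 and 8 incidents per 1000.

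- Ward-weeks: 24 × 68 = 1,632, so 244,800 / 1,632 = 150 bed days per ward-week.
- After omission: 1,632 − 24 × 3 = 1,560. Control: 8 × (14 + 31 + 48) = 744. Intervention: 8 × (51 + 34 + 17) = 816.

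**Assumptions, because the article is silent.** Two-sided 5%; 80% power (z total 1.960 + 0.842 = 2.802); ICC read as log-scale ward variance τ² of 0.03–0.08; 12% paired with 8/1000 and 28% with 2/1000.

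**Step 1: reproduce the stated range.** Split the bed days into two halves of 122,400, with no time effect and no ward effect. For a reduction θ, SE(log RR) = √(1/E₀ + 1/E₁), with E₁ = E₀(1 − θ), and solve −ln(1 − θ) = z × SE.

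- 8/1000: E₀ = 979.2. At 80% power E₁ = 859.0, SE = 0.0467, θ = 12.3%. At 90% power, 14.1%.
- 2/1000: E₀ = 244.8. At 80% power E₁ = 186.4, SE = 0.0972, θ = 23.8%. At 90% power, 27.3%.

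This comes close to 12–28%.

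**Step 2: the planned model.** For ward i in week t, the expected count μ is 150 × rate, multiplied by (1 − θ) once the intervention has started. With a ward random intercept, the information is the sum over wards of X′WX − [τ² / (1 + τ²Σμ)] (X′μ)(X′μ)′, where W is diagonal in μ. X holds the intervention, an intercept and the time terms. SE is the square root of the intervention entry of the inverse. Again solve −ln(1 − θ) = 2.802 × SE.

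| Time effect | 8/1000 | 2/1000 |
|---|---|---|
| none | 13–14% | 25–26% |
| linear | 21–22% | 37–39% |
| 17-week period | 22–23% | 38–40% |
| weekly | 22–23% | 39–40% |

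Ranges run over τ² 0.03–0.08; before rounding, the largest value (weekly, 2/1000) is 40.5%, so the overall span is 21–23% and 37–41%. Example (period effects, 8/1000, τ² = 0.03): SE = 0.0868, 2.802 × 0.0868 = 0.243, and 1 − e^(−0.243) = 21.6%.

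Against the stated figures: 21/12 = 1.75 and 23/12 = 1.92; 37/28 = 1.32 and 41/28 = 1.46. The range is about 1.3–1.9 times.

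**Step 3: power at the stated effects (period effects).**

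- 12% at 8/1000: −ln(0.88) = 0.128; SE 0.0846–0.0884; power about 30–33%.
- 28% at 2/1000: −ln(0.72) = 0.329; SE 0.164–0.173; power about 48–52%.

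A 1,500-run simulation with ward fixed effects (ward variance 0.08) gave 71% without and 29% with period effects for the first case, and 86% and 39% for the second.

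**Step 4: other readings.**

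- One-sided 5%: 19–20% and 33–36%.
- 244,800 read as the 51 weeks only (200 per ward-week, 326,400 in all): 19–20% and 33–36%.
- 90% power: 24–26% and 42–46%.

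**Step 5: the composite.** Its rate is not given. If the three named outcomes lie within 2–8/1000 and span that range, they sum to between 2 + 2 + 8 = 12 and 2 + 8 + 8 = 18, before Code Blue calls, intensive care admissions and other falls. The planned model then detects about 15–19%, without overdispersion. At an assumed 16/1000 it detects about 16–17%. Assumed overdispersion of 1.5–2 raises the 12–18/1000 range to about 19–26%.

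**The case against.** The strongest objection is that the basis of 12–28% is not shown. A condensed article can leave the significance level and power to the full protocol, and it cites the feasibility study, which is not at hand. This stands in part: strict reproduction is impossible. But the point is not an omission. A specific figure is printed beside a model that, on conventional assumptions, does not deliver it.

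A reader might infer that 12% is out of reach on any basis. The article does not support that. It collects three years of pre-trial data to study seasonal and temporal effects. If a linear trend were fitted jointly to about 140 further weeks of such data, the detectable reductions would be about 12.6% and 24%. Two things limit this rescue: the section sets the analysis period at 68 weeks, and with categorical time the gain is small (about 20% and 37–38%). It is a possible basis, not a stated one.

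A reader might also infer that the primary analysis is underpowered. That is not shown: the composite rate is higher than any component rate, and the 16–17% above lies inside the stated range, though not at its 12% end.

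Finally, "All patients admitted or transferred to one of the study wards during the trial period will be included in the primary analysis" could be taken to confine the analysis to 51 weeks. The sentence just before it sets 68 weeks with the control period, so that reading fails. Nor is it a contradiction that the expected sample may count weeks later omitted; 72 of 1,632 ward-weeks (4.4%) is minor.

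**Conclusion.** The point holds for the stated component figures. The loss comes mainly from fitting the secular trend and depends little on the ward variance, so the unstated ICC scale does not explain the gap. The sizes given above rest on the assumed two-sided 5%, 80% power, log-scale ward variance, pairing of rates with effects and a 68-week fit without the earlier pre-trial data. The alternatives in Step 4 move the figures by a few points and do not restore 12–28%.

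Separately, the power statement rests on outcomes that the article makes secondary, and it takes only falls occasioning harm where the composite counts all falls. The primary outcome has no stated detectable difference. That gap says nothing either way about whether its power is adequate.

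**What to change.** Recompute the detectable rate ratio under the planned Poisson mixed model, stating the form of the time effect and including the ward random effect and the omitted weeks. Give it first for the composite, with its assumed baseline rate, ward variance and its scale, significance level and power. Label any component figures as secondary, each with its own rate and effect.

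Overdispersion or ward-by-period variance can be added as a sensitivity case; neither is part of the model as written.

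If 12–28% relied on the three-year pre-trial series, say so and write the analysis model so that it includes those data.

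The cost is one paragraph and a less favourable stated figure. No extra wards or patients are needed.

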Nurses play a central role in patient safety by conducting physical assessments and communicating findings to the multidisciplinary team, and implementing and evaluating the effect of nursing clinical interventions. Minimal vital signs datasets inform physiological tracking systems that determine the need for urgent patient interventions [4], and aberrations in vital signs must be recognised and acted upon to trigger medical rescue models such as rapid response systems and medical emergency teams [18]. Such approaches have been shown to decrease in-hospital mortality; however, patients who meet rapid response criteria still often require admission to intensive care and typically exhibit advanced physiological deterioration [19]. Reliance on vital signs alone creates a critical gap in nursing practice, in that patient deterioration is approached reactively rather than proactively [20, 21] and nurses’ capacity for critical decision making may be reduced [22]. Shifting to comprehensive and systematic physical assessments has the potential to identify, address and mitigate clinical deterioration, falls, and pressure injuries earlier in the deterioration process [23–25].

Complementary to improving nursing assessment practices, effective nurse-to-nurse and nurse-to-medical officer communication is essential for patient safety [7]. Clinical handovers are one of the most frequent and significant communicative processes between clinicians [26], but an estimated 80% of adverse events involve miscommunication during handover [10]. Recognised as a priority internationally [27], the Australian National Safety and Quality Health Service Standards encourage structuring handover using clinical communication frameworks, and conducting handovers at the bedside to support patient and caregiver involvement [11]. Upon recognising potential risks to patient safety, effective multidisciplinary communication practices are an essential mechanism to facilitate early escalation and actioning of treatment pathways [28]. Contextual (e.g. ward/hospital culture, hierarchies within organisations/disciplines) and personal factors (e.g. individual attitudes, team dynamics) have been observed to influence whether or not concerns are raised, and must be overcome to achieve effective communication [29].

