### Cost–benefit analysis

Economic evaluation of the ACCELERATE Plus intervention compared with usual care will be assessed using a cost–benefit analysis. Resource use and cost of intervention will incorporate the involvement of staff, equipment hire and other materials for clinician training and related activities. The intervention’s effect on the primary outcome (medical emergency team calls, unplanned intensive care unit admissions, falls and pressure injuries) will be valued in monetary terms using the Australian unit costs obtained from Australia’s Independent Health and Aged Care Pricing Authority (formerly known as Independent Hospital Pricing Authority (IHPA)) and previous published/unpublished work [9]. Results for the cost–benefit analysis will be reported as the benefit-to-cost ratio; if the benefit-to-cost ratio is greater than 1, the intervention will be considered of value. To examine the robustness of results, sensitivity analyses will be conducted.

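### The primary Poisson model makes no allowance for calls, Code Blues and ICU transfers that cluster within one patient, so its standard error is likely too small

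*Protocol article*

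**What the plan says.** The Protocol article, under Outcome measures (Primary), builds the primary outcome from four parts: emergency-team calls (rapid response and Code Blue), unplanned ICU admissions, falls and pressure injuries. The ICU part is defined as "patients unexpectedly requiring transfer from participating wards to the intensive care unit". Transfers that follow a call are not set apart.

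The Data analysis section repeats the composite and fixes the model: "Patient outcome data will be modelled as counts using Poisson regression with an offset for time on ward". On structure it adds that "we will use fixed effects for secular trend, and a random effect for ward". It names no patient or episode effect, dispersion parameter or robust variance. The secondary analyses in that section (change over time, demographic covariates, comorbidity) do not supply one.

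The Background says of rapid response systems in general that "patients who meet rapid response criteria still often require admission to intensive care and typically exhibit advanced physiological deterioration". No proportion is given.

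**The concern.** Given the ward effect and the fixed effects, a Poisson model sets the variance of each count equal to its mean. That holds if events arrive singly and independently. It fails if one deterioration brings a call, then a Code Blue, then an ICU transfer, or if one unstable patient triggers several calls. The events then arrive in clumps.

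A random intercept for ward takes up stable differences between wards. It does not take up clumping within patients. The estimated rate ratio for total events is not biased by this, but its standard error is too small, its confidence interval too narrow and its false-positive rate above nominal. This affects the trial's primary test.

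**Working it through.** **The plan's own figure.** The stated detectable difference of 12–28% rests on rates of 2–8 per 1000 bed days for single components, so it does not test this point. A plain two-sample Poisson formula with 244,800 bed days split equally gives 12.3% (rate 8) to 23.8% (rate 2) at 80% power, and 14.1% to 27.3% at 90%. Alpha, power and the scale of the intra-cluster correlation are not stated, so the figure can be neither confirmed nor called wrong.

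**Inputs.** From the article: Poisson counts, a random effect for ward only, and overlap between calls and ICU admission described as frequent. Assumed, because the article does not give them: a two-sided 5% test; a share p of deteriorations that produce two counts instead of one; and, for the full composite, 8 deteriorations to 4 single-count falls or pressure injuries per 1000 bed days.

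**Step 1: dispersion.** Let K be the number of counts per deterioration. The variance-to-mean ratio is φ = E[K²]/E[K].
- Deterioration events alone: E[K] = 1 + p and E[K²] = (1 − p) + 4p = 1 + 3p, so φ = (1 + 3p)/(1 + p).
- Full composite: φ = [8(1 + 3p) + 4]/[8(1 + p) + 4].

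**Step 2: effect on the test.** The true standard error is √φ times the Poisson one. Actual type I error = 2[1 − Φ(1.96/√φ)].

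| Events | p | φ | √φ | Type I error |
|---|---|---|---|---|
| Deterioration only | 10% | 1.3/1.1 = 1.18 | 1.09 | 7.1% |
| Deterioration only | 20% | 1.6/1.2 = 1.33 | 1.15 | 9.0% |
| Full composite | 10% | 14.4/12.8 = 1.13 | 1.06 | 6.5% |
| Full composite | 20% | 16.8/13.6 = 1.24 | 1.11 | 7.8% |

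A heavier assumption, 25% pairs plus 10% triples, gives φ = 2.55/1.45 = 1.76 and 13.9% for deterioration events alone. For the composite it gives 24.4/15.6 = 1.56 and 11.7%. This is a stress case only.

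**Step 3: simulation.** The layout was 24 wards, three sequences, 68 weeks, the three omitted weeks, and 244,800/(24 × 68) = 150 bed days per ward-week. It used 8 deteriorations per 1000 bed days, no treatment effect and 1,500 runs. Ward fixed effects stood in for the random intercept. Deterioration events only:

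| Linkage | Plain Poisson | Scaled by Pearson dispersion |
|---|---|---|
| None | 5.2% | 4.1% |
| 20% pairs | 9.7% | 4.9% |
| 25% pairs, 10% triples | 13.7% | 4.7% |

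Monte Carlo uncertainty at 9.7% is about ±1.5 points (1.96 × √(0.097 × 0.903/1500)).

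A separate run of the planned mixed model had 20% of events doubled, an assumed rate of 16 per 1000 and 500 runs. It rejected in 9.2%. The empirical SD was 0.069 against a mean model standard error of 0.059, a ratio of 1.17, close to the 1.15 from the formula. The excess therefore comes from the linkage, and a dispersion allowance removes it.

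**The case against.** The strongest reply is that the article never says how linked events are counted, and that linkage rules and dispersion checks are usual content for the statistical analysis plan. The article promises such a plan before data lock, and it is not shown. That much stands: the missing counting rule is no finding in itself, and separate counting is the natural reading but not a stated rule. It does not dispose of the point, because the distribution and the random effect are stated. The later plan would have to change the stated model, not merely add detail.

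It is also fair that the Background sentence describes rapid response systems in general. It supports overlap as plausible but does not measure it in these wards. The size of the effect is therefore conditional throughout.

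Three stronger readings are tempting, and the documents do not support them.
- **Linked episodes are costed twice.** The Cost–benefit analysis says that the effect on "medical emergency team calls, unplanned intensive care unit admissions, falls and pressure injuries) will be valued in monetary terms". A call and an ICU stay use different resources, so pricing both is double counting only if their unit costs overlap. Nothing says that they will. The per-case cost of deterioration in the Background is not named as the unit cost to be used.
- **Linked events must be collapsed in the primary outcome.** Total event burden is a legitimate target, and the trial hypothesises fewer calls and fewer ICU admissions. If a call and the transfer that follows count once, preventing that transfer leaves the composite unchanged.
- **Repeat calls make the error far larger.** They would add dispersion, but the article gives no figure from which to say how much.

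**Conclusion.** The point holds in conditional form. The article fixes a plain Poisson mixed model with a ward effect only, for a composite whose components can share one deterioration by the article's own account. If each event is counted, the standard error is too small.

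With 10–20% of deteriorations producing one extra count, the composite's true standard error is about 6–11% larger than the model reports, and type I error is about 6.5–8% instead of 5%. For deterioration events alone, the figures are about 9–15% and 7–9%. The overlap share, the 8:4 mix and the 5% level are assumptions. Repeat calls are not included and would add to the excess. The misstatement is moderate, but it falls on the primary test and always in the direction of too much certainty.

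**What to change.** In the primary model, replace plain Poisson with a specification that allows overdispersion, and name it in the statistical analysis plan before data lock. Any one of these would serve:
- a negative binomial mixed model;
- the Poisson mixed model with an added observation-level random effect, or with a patient-episode random effect if the analysis is run at patient level;
- dispersion-scaled or robust standard errors. Robust errors clustered on only 24 wards would need a small-sample correction.

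Keep the composite as defined. A sensitivity analysis that counts linked events in one patient as a single episode can be added to show how far the result depends on cascades.

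The change needs no new data for the primary analysis. The cost is a somewhat wider interval, about 6–11% for the composite in the assumed range. If there is little linkage, the estimated dispersion will be near 1 and the loss small: the simulated scaled test rejected in 4.1% with no linkage, so it was slightly conservative. The sensitivity analysis needs event dates and times linked within patient.

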### Design

A pragmatic, hybrid type 1, stepped-wedge cluster randomised trial design will be conducted [32] with a cost–benefit analysis and qualitative process evaluation. The hybrid type 1 trial design allows the evaluation of intervention implementation concurrent to the primary clinical efficacy outcomes. Combining these data produces more useful information for decision-makers aiming to promote the more rapid translation of evidence to practice [33]. As our trial involves enhancement of current best practice, a stepped-wedge design is desirable as all participants eventually receive the intervention. The trial intervention, implementation and evaluation are informed by the Medical Research Council Framework for complex interventions [34] and evidence-based implementation strategies [35].

The trial intervention will be sequentially implemented over three periods of 17 weeks, totalling 51 weeks. A total of 24 wards will be enrolled to the trial, with eight sites each contributing three wards (Fig. 2).

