### Randomisation

Wards will be stratified by hospital and randomly allocated to one of the three sequences. Planned stratified allocation is shown in Fig. 2. Randomisation will be computer-generated and performed by a blinded researcher not involved in the trial.

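### The stated primary model has no term for ward-specific change between periods, so its standard error is too small, and type I error exceeds 5%, if wards drift independently

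*Protocol article*

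**What the plan says.** The Data analysis section of the protocol article sets the outcome model: "Patient outcome data will be modelled as counts using Poisson regression with an offset for time on ward". On the mixed-model structure it says: "we will use fixed effects for secular trend, and a random effect for ward". It names no ward-by-period effect, random slope, overdispersion term or robust variance.

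The layout comes from three places:
- Design: "A total of 24 wards will be enrolled to the trial, with eight sites each contributing three wards".
- Randomisation: "Wards will be stratified by hospital and randomly allocated to one of the three sequences".
- Data analysis: 68 weeks, "comprising 51-week trial period and an additional 17-week control period prior to the first step", less "the three weeks immediately prior which will be omitted from the analysis as a period for implementation of the intervention".

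The planning inputs are "We expect to collect data from 48,960 patient episodes of care representing 244,800 bed days" and "intra-cluster correlation = 0.03–0.08, baseline rate = 2–8 incidents/1000 bed days". Only one intra-cluster correlation range is given. There is no cluster autocorrelation or between-period variance, and no rate for the composite.

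The same section provides for adjustment for patient characteristics, a look at three years of pre-trial data for temporal patterns, secondary analyses, and a statistical analysis plan to be completed before data lock.

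**The concern.** The model as worded assumes that all 24 wards follow one common time course, that each departs from it by a fixed multiple, and that everything else is Poisson noise. Over 68 weeks a ward's staffing, case mix and incident reporting can change for reasons of its own. The eligible wards are medical, surgical and rehabilitation wards, and the Strengths and limitations section itself lists consistency of the routine data as a consideration.

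Every ward crosses from control to intervention, so the effect estimate rests largely on within-ward change. Ward-specific movement feeds into that estimate, and a Poisson variance with only a ward intercept cannot expand to reflect it. The interval would then be too narrow, and ordinary ward drift could be declared a significant effect on the primary outcome. The same effect estimate is carried into the cost–benefit ratio.

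**Working it through.** **The plan's own figure.** The article states no type I error. Its only related figure is a detectable difference of 12–28%, with no alpha, power or pairing of rate with ICC. Taking two-sided 5% and 80% power:
- An unclustered comparison of two halves of 122,400 bed days has SE = √(2/events per half). At 8/1000 this is √(2/979.2) = 0.0452, giving 1 − exp(−2.802 × 0.0452) = 11.9%. At 2/1000 it is √(2/244.8) = 0.0904, giving 22.4%.
- A stepped-wedge model with a ward intercept and time effects gives about 22% at 8/1000 and 38% at 2/1000.

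Neither matches the whole range. The figure cannot be verified from what is stated; that does not show it to be wrong, and nothing below depends on it.

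**Inputs from the article.** 24 wards; 4 × 17 = 68 weeks; 3 weeks dropped before each ward's start, so 14/17 of that period is kept; 244,800/(24 × 4) = 2,550 bed days per ward-period, or 150 per ward-week.

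**Assumptions.** Eight wards per sequence, one per hospital (Fig. 2 is not shown); bed days spread over all 68 weeks; ward log-SD 0.5 (using 0.4 moves the error rates by about 0.1 point); an independent ward-by-period effect with log-SD s; event rates of 2, 8 and 16 per 1000. The first two rates are the ends of the stated range for components. The third is an assumed composite rate.

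**Why the rate matters.** The Poisson variance of a ward-period log rate is 1/events: 1/5.1 = 0.196 at 2/1000, 1/20.4 = 0.049 at 8/1000 and 1/40.8 = 0.0245 at 16/1000. With s = 0.20 the unmodelled variance is 0.04. That is small against the first, similar to the second and larger than the third.

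**Method.** Generalised least squares on log rates with four period effects, the intervention effect and a ward intercept. Let V be the covariance the model assumes (ward intercept plus Poisson variance), E = s² on each ward-period, and D the design matrix.
- Model variance: A = (D′V⁻¹D)⁻¹.
- True variance: A D′V⁻¹(V + E)V⁻¹D A.
- Type I error: 2Φ(−1.96 × SE_model/SE_true).

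Example at 8/1000, s = 0.20: 0.0880/0.1159 = 0.759, and 2Φ(−1.488) = 13.7%. At 16/1000: 0.0627/0.0989 = 0.634, and 2Φ(−1.243) = 21.4%.

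| Rate per 1000 | s = 0.05 | 0.10 | 0.15 | 0.20 |
|---|---|---|---|---|
| 2 | 5.1% | 5.5% | 6.1% | 7.0% |
| 8 | 5.5% | 7.2% | 9.9% | 13.7% |
| 16 (assumed) | 6.1% | 9.4% | 14.8% | 21.4% |

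If the bed-day total covers only 51 weeks (3,400 per ward-period), the values at s = 0.10, 0.15 and 0.20 become 7.9, 11.6 and 16.4% at 8/1000, and 10.9, 17.8 and 25.7% at 16/1000.

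**Simulation check.** Poisson ward-intercept models were fitted to simulated data with ward log-SD 0.4 and 500 runs per setting (Monte Carlo SE 1–2 points). For s = 0.05, 0.10 and 0.20 they gave 7.4, 10.2 and 16.0% at 8/1000, and 5.8, 8.8 and 26.6% at 16/1000. With s = 0 they gave 4.6–5.0%. A separate 800-run simulation at s = 0.15 gave 11.9% and 18.1%. The simulations are mostly somewhat above the analytic values.

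**Drift shared within a hospital.** At s = 0.15 with ward log-SD 0.4, the error is 9.9% at 8/1000 if all drift is ward-specific, 7.4% if half of its variance is common to the hospital, and 5.0% if all is. At 16/1000 the values are 14.7, 9.9 and 5.0%.

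**The case against.** The strongest reply is that this is a condensed article. The model sentence does not even mention the intervention term, so it is not a complete specification, and the announced analysis plan may add the missing variation. That is fair, and nothing in the article forbids the extra term. But the article does name the random-effects structure, and anyone following it as worded would fit a ward intercept alone. The demographic adjustment and the review of pre-trial data may reduce drift caused by case mix. They do not give the model a variance for what remains.

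The second reply concerns size, and it stands. A reader might infer that any ward movement inflates the error two- to fourfold, or that the primary test simply fails to hold 5%. The documents support neither. At s = 0.05 the analytic error is 5.1–6.1% at all three rates, and at 2/1000 it stays at or below about 7% up to s = 0.20. Reaching 10% to 20% needs s of about 0.15–0.27 at 8/1000, or 0.11–0.19 at 16/1000. The article gives neither s nor the composite rate.

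The quoted ICC does not settle the matter. Read as a log-scale ward variance, it implies only 5.3–8.3% at 8/1000 over assumed cluster autocorrelations of 0.95 to 0.8. Read as an episode-level ICC over the same autocorrelations, it implies about 13–49%.

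A reader might also object that hospital, the randomisation stratum, is missing from the model. That is of little consequence. Ward intercepts absorb constant hospital differences, and drift common to a hospital cancels in the balanced layout assumed here.

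**Conclusion.** The point holds conditionally. The stated structure has nothing to absorb ward-specific change between periods, so its standard error is too small whenever such change exists. At s = 0.20 the true SE is 1.32 times the reported one at 8/1000 and 1.58 times at 16/1000. For s between 0.10 and 0.20 the analytic type I error is about 7–14% at 8/1000 and 9–21% at the assumed 16/1000. With little drift, low rates or hospital-wide drift it stays close to 5%.

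The 2/1000 row is the less relevant one for the primary outcome. If component events are summed, the composite rate cannot fall below that of its most frequent component. The composite rate itself is still unknown. All these figures assume independent drift, equal exposure per ward and one ward per hospital in each sequence.

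**What to change.** State the primary model as a Poisson mixed model with time fixed effects, the intervention effect, a ward random intercept and a ward-by-period random intercept. This is one additional term in lme4, the software already planned. Optionally, confirm the result with a permutation test that reassigns sequences within hospital, as randomised. The three years of pre-trial data can be used to estimate the between-period SD before the analysis plan is finalised.

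In simulation (300 runs each, Monte Carlo SE about 1.3 points) the added term gave a type I error of 6.3% at 8/1000 and 4.3% at 16/1000 with s = 0.20, and 5.0% at 8/1000 with s = 0.

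The cost is precision when the variation is real. Detectable reduction at 80% power is 1 − exp(−2.802 × SE):
- At 8/1000, going from s = 0 to s = 0.20 raises the SE from 0.0880 to 0.1154 and the detectable reduction from 21.9% to 27.6%.
- At 16/1000, the SE rises from 0.0627 to 0.0982 and the detectable reduction from 16.1% to 24.0%.
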